The role of CAD as applied to chest x-rays is to minimize the potential errors by the interpreter and to identify potential cancerous lesions that can be missed. By improving the accuracy and consistency of radiological diagnosis, CAD will assist the radiologist in detecting early disease that can be potentially missed, allowing for early intervention and management16. We propose to use one of these systems in a screening setting. This will be the first controlled trial of chest x-ray screening in which there is a placebo control group, and the first chest x-ray screening trial that uses CAD to improve our ability to detect subtle cancers.

3.0 **OBJECTIVES**

3.1 **PRIMARY OBJECTIVE**

The primary aim of the study is to report and compare the frequency of advanced-stage lung cancers at the end of the 2 ½ year study between screened and placebo groups.

3.2 **SECONDARY OBJECTIVES**

The secondary aims are as follows:

- Determine whether lung cancer screening with chest x-rays and computer aided detection (CAD) reduces the incidence of symptomatic advanced lung cancer compared to no screening in a high-risk population. The presence of advanced symptomatic lung cancer will be determined by the Outcomes Review Committee.
- Compare the disease-specific mortality between screening with chest x-ray and CAD versus no screening. This is the endpoint used in many RCTs of lung cancer screening; thus, we will be able to compare our study results to the results of these other trials.
- Compare the all-cause mortality rate between screening with chest x-ray and CAD versus no screening. This endpoint includes all deaths including those attributed directly and indirectly to screening.
- Compare the length of time between randomization and the incidence of symptomatic advanced lung cancer for screened subjects versus controls. This analysis will provide data about how screening might delay the development of advanced lung cancer.
- Measure the monetary cost relative to the quality of life between screening with chest x-ray and CAD versus no screening. The comparison of quality of life since randomization between the two study arms will reveal differences over time due to screening. Coupled with an assessment of monetary costs, cost-utility of screening will be measured. Note that the cost-utility analysis will be performed on a subset of the study participants.

4.0 **SELECTION OF PATIENTS**

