At the time of study enrollment and at the annual screen, subjects will be given a packet of study forms (see table 1) and a pre-addressed envelope to take home. The study forms are to be completed by the subject at home and returned to the study trained research personnel at six-month intervals. If the study subject does not return the forms within 2 weeks of the scheduled completion date, the study trained research personnel will phone the subject and administer the study questionnaires via telephone. The study trained research personnel will review the study forms for completeness. If the study trained research personnel have questions about the study form, then the study trained research personnel will call the subject for clarification before sending the study form for data entry into the database.

If at anytime during the duration of the study, the subject is diagnosed with lung cancer additional follow-up will be obtained regarding the diagnosis, pathology staging, treatment, complications and mortality at 2 months intervals. This information will be obtained via telephone or mail by the study trained research personel.

11.0 **RECORD KEEPING**

Records will be secured and kept per all institutional, NCI, state and Federal regulations.

11.1 **DATA COLLECTION FORMS**

The forms to be completed by the study subjects are attached as appendices to this protocol.

Potential trial participants will call into the trial hotline number. Trained research personnel will obtain information to screen for possible eligibility and collect contact information for study appointment. The investigator complies and agrees the protected health Information (PHI) collected to identify eligibility of candidates adheres to the following three criteria: is necessary for the purpose of this research, will be used solely for this research, and will not leave The Cleveland Clinic Health System (CCHS).

The authorization for the release of medical information form will be signed by all subjects at the time of randomization. Attempts to obtain the authorization will be made every six months, but will be required yearly. We will be able to capture changes to their medical insurance provider on a yearly basis.

The eligibility form will be completed to confirm that the subject meets inclusion and exclusion criteria prior to enrolling subject into research trial. Patient informed consent will be signed prior to randomization.

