The primary outcome measure is the frequency of advanced-stage cancers detected during the course of the 2 ½ year study. These advanced-stage cancers may be detected during the study's planned screenings, through progression of preclinical disease to clinical symptomatic disease, and, less frequently, during medical testing/screening for other purposes (e.g. presurgical work-up). Advanced-stage cancers will be defined as stage III or IV cancers and will be assessed as clinically indicated, which usually includes PET imaging, additional invasive testing (i.e. tissue sampling), and sometimes brain imaging.

12.2 **SECONDARY ENDPOINT ASSESSMENT**

A secondary endpoint is the presence/absence of symptomatic lung cancer. To assess this outcome, an expert outcome review committee, consisting of a pulmonologist and an oncologist, will be convened at the end of the study (after March 2011). The committee members, each working independently, will review all cases of diagnosed, pathology-proven lung cancer as well as all deaths. Committee members will be blinded to the randomization assignment of the subjects and results of screening tests. Based on the subject’s self-reported symptoms assessment during the study and their medical records, and death certificates (if appropriate and available) the committee members will determine whether the subject is asymptomatic or has symptoms that correlate with their diagnosis of lung cancer. Subjects determined to have symptoms of lung cancer by both committee members will be classified as events for calculation of this secondary endpoint. In cases where the two committee members disagree, the committee members will meet to discuss the cases and reach consensus. Deaths due to lung cancer and deaths due to the management or treatment of diagnosed lung cancer will also be classified as events. For all events, committee members will decide on, to within 6 months, the time at which the subject developed symptoms.

Note that for the assessment of the primary and secondary endpoints, subjects who are determined to have lung cancer that has metastasized will be considered a censored event at the time of diagnosis. These subjects’ lung cancer will not be classified as events in the assessment of the primary and secondary endpoints.

Definition of "Advanced Symptomatic Disease":

The following criteria will be assessed by the Outcomes Review. All three criteria must hold.

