1. The patient has been diagnosed with non-small cell carcinoma, stage II or

higher, or small cell carcinoma, any stage.

2. The patient has experienced a symptom that led them to seek contact with a

physician since the time of the last study visit; or at the time of their next study

visit, the patient has developed a new symptom or a change in a chronic

symptom within the past 6 weeks, that did not yet lead to a doctor's visit.

3. The symptom(s) described in #2 are felt to be related to the diagnosis of lung

cancer as adjudicated by the Outcomes Review Committee.

For the other secondary endpoints, the committee will review the medical records and self-reported symptoms assessment of all deaths and determine if the death is due to lung cancer.

13.0 **STATISTICAL ANALYSIS PLAN**

13.1 **PRIMARY AIMS:**

Analyses will be based on an intent-to-treat perspective. We will test the null hypothesis that at the time of diagnosis the frequency of advanced-stage cancers is the same for screened and unscreened groups; the alternative hypothesis is that the frequency of advanced-stage cancers is different for screened and unscreened groups. These hypotheses will be tested at the end of the two and a half-year study, i.e. after March 31, 2011. The frequency of advanced-stage cancers in the two study arms will be compared using logistic regression analysis. A model will be fit to describe the probability of advanced-stage cancer as a function of the following independent variables: age, gender, symptoms status at the time of enrollment into the study (i.e. symptoms present or not present), study arm, and two-way interactions with study arm. The fit of the model will be assessed using the Hosmer-Lemeshaw goodness of fit test. The coefficients for study arm and interactions with study arm will be assessed, after adjusting for other covariates, using a likelihood ratio test with significance level of 0.05 (two-tailed).

13.2 **SECONDARY AIMS:**

One of the secondary aims of the study is to determine whether lung cancer screening using chest x-rays and CAD reduces the incidence of symptomatic advanced lung cancer relative to no screening. The observed cumulative incidence of symptomatic advanced lung cancer, measured in events per person per years observed, will be compared between the two study arms. The analysis will be carried out from an intent-to-treat perspective.

The incidence rate of symptomatic lung cancer will be estimated as follows

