Incidence rate at time *t*= [# events by *t*] / [# of person-years at risk until *t*].

where “event” is the development of symptoms due to lung cancer or death due to treatment for the disease or lung cancer death (whichever is observed first). These events will be determined by the outcome review committee at the end of the study (after March 2011). The number of person-years at risk is equal to t – e, where t is the smaller of [time at which the subject experienced symptoms of lung cancer, time at which the subject was lost to follow-up if the subject did not die from lung cancer or from its treatment before *t*, time at which the subject died from lung cancer or its treatment, *t*], and

e is the number of study months before the subject was enrolled into the study (i.e. e=0 at the start of the study).

The following null hypothesis will be tested: the incidence rates of the screened and control subjects are equal. The alternative hypothesis is the incidence rates of the screened and control subjects are not equal. A stratified analysis will be used. There will be four strata:

- age < 65 years at enrollment; none/mild pulmonary symptoms at enrollment
- age > 65 years at enrollment; none/mild pulmonary symptoms at enrollment
- age < 65 years at enrollment; moderate pulmonary symptoms at enrollment
- age > 65 years at enrollment; moderate pulmonary symptoms at enrollment.

Note that only four strata were chosen because the overall number of events will be small. These particular four strata were chosen because we expect that age and pulmonary health at enrollment are the strongest predictors of the development of lung cancer and curability of lung cancer.

For each stratum i, the data can be summarized as follows:

Screened Control Total

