# events a1i a0i Mi

Person-years N1i N0i Ti

______________________________________________________________________________

The Mantel-Haenszel rate ratio19 is given by

RR=[a1iN0i/Ti] / [a0iN1i/Ti].

The variance of the ln(RR) is given by20

Var[ln(RR)] = [MiN1iN0i/Ti2] / [(a1iN0i/Ti)(a0iN1i/Ti)].

The 95% CI for RR is as follows:

lower = exp[ln(RR) – zval * Var(ln(RR))1/2

upper = exp[ln(RR) + zval * Var(ln(RR))1/2,

where zval is the value from the standard normal distribution whose value will depend on the time of the analysis (see subsection on Interim Analyses).

If the 95% CI for RR does not include the value one, then we will reject the null hypothesis.

The analyses described above for the cumulative incidence of symptomatic advanced disease will also be performed for disease-specific mortality and all-cause mortality.

A Cox proportional hazards model will be fit to compare the two study arms on the time from randomization until symptomatic disease. Covariates will be included in the model, such as age, gender, race, smoking history, symptoms at presentation, as well as site of enrollment. A significance level of 0.05 will be applied.

13.3 **OTHER ANALYSES:**

In the intervention arm, for each screening, we will report the number of subjects with actionable findings and the type of findings. We will report the follow-up results of these findings. This will provide data on the false positive rate and the size and stage of detected cancerous nodules.

We will test the effect of CAD on radiologist performance. This will include the effect of CAD on the radiologists’ sensitivity, as well as the effect on the false positive rate. First, we will separate the screened cases into one of three groups based on follow-up results, as available: cancerous nodule(s) present, benign nodule(s) present and no cancerous nodules present, no nodules present. For each group we will compare the frequency with which radiologists reported an actionable nodule without CAD versus with CAD. For each group the frequencies will be compared using a McNemar’s test, modified for clustered data.21  The modification is necessary because two radiologists will be interpreting each case. A significance level of 0.05 will be applied.

14.0 **SAMPLE SIZE CONSIDERATIONS**

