The Markov decision tree model will be used to derive the long-term cost-effectiveness differences between lung cancer screening and placebo screening for 10 and 20 years. The transition cycle of the Markov model will be one year. The transitional probabilities between different disease states will be calculated from the collected incidence of the study. The cost and utility data of the Markov model will apply the data from the five-year study period by discounting of 3% as a base-case. Similarly, ICERs will be calculated and bootstrap simulation will be used to derive the 95% confidence intervals of the ICER.

Sensitivity analysis will be performed by varying costs and utilities by their 95% confidence intervals established in our study. The impact of varying the probabilities of the detection of pre-clinical disease and incidental findings will also be investigated in sensitivity analysis. Sub-group analysis will also be used to investigate the patient characteristics that could contribute to the most cost-effective use of screening, including age, gender, and smoking history.

16.0 **ADVERSE EVENTS**

The principal investigator/s will review all adverse events and unanticipated problems as related to the imaging research. Adverse events and unanticipated problems will be reported promptly per all institutional, FDA, state and Federal regulations. In addition, if the investigator and co-investigators as a group have any concerns, they will escalate those concerns to the outside advisory board for review and guidance.

Adverse event reporting is to be distinguished from the collection of data for purposes of analyzing trial endpoints, which is achieved through the recording of specific data elements on case report forms and statistical analysis.

Complications associated with primary interventions are termed direct AE's. Screening tests promote downstream diagnostic interventions: complications associated with these diagnostic interventions are termed indirect AE's. Primary interventions in this protocol are the screening chest x-ray or placebo. In this protocol only direct adverse events associated with the primary trial intervention (chest x-ray or placebo) will be reported as adverse events. Indirect adverse events (complications associated with these diagnostic interventions) will be documented as part of the endpoints on case report forms.

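### Section 12.2 asks only whether a death is due to lung cancer, so disease-specific mortality, read literally, omits treatment and work-up deaths that the protocol elsewhere counts or names separately; this could favour the screened arm

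*Protocol*

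**What the plan says.** Protocol section 3.2 lists disease-specific mortality as a secondary aim: "Compare the disease-specific mortality between screening with chest x-ray and CAD versus no screening". It gives comparability with other lung cancer screening trials as the reason. All-cause mortality is a separate aim there, described as covering every death, including those that screening caused directly or indirectly.

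Section 12.2 sets two adjudication rules for deaths.

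- Symptomatic lung cancer: "Deaths due to lung cancer and deaths due to the management or treatment of diagnosed lung cancer will also be classified as events".
- Disease-specific mortality and the rest of the secondary list: "the committee will review the medical records and self-reported symptoms assessment of all deaths and determine if the death is due to lung cancer".

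Section 13.2 defines an event in the incidence-rate analysis as "development of symptoms due to lung cancer or death due to treatment for the disease or lung cancer death". On the mortality endpoints it adds: "The analyses described above for the cumulative incidence of symptomatic advanced disease will also be performed for disease-specific mortality and all-cause mortality". It does not restate which deaths then count.

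On complications of diagnostic procedures, section 16.0 says: "Indirect adverse events (complications associated with these diagnostic interventions) will be documented as part of the endpoints on case report forms".

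**The concern.** Within one section, the same committee is given a wide rule for one endpoint and a narrower one for another. Nothing says whether the difference is intended. Section 13.2 treats death from treatment and death from lung cancer as two items, so in the protocol's own vocabulary a treatment death is not a lung cancer death.

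The deaths at issue are ones that screening may itself produce: deaths after treatment of a cancer found early, and deaths after invasive work-up of a shadow that is not cancer. If more of them occur in the screened arm and they are not counted, the disease-specific comparison looks better for screening than it should. Two committee members working independently could also apply different rules to the same death.

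**Working it through.** The protocol gives no event count or power for disease-specific mortality, so there is no planned figure to reproduce. The check is a comparison of definitions, followed by an illustration of scale.

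**Which deaths count where**

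| Cause of death | Symptomatic cancer (12.2, 13.2) | Disease-specific mortality (12.2, literal) | All-cause mortality (3.2) |
|---|---|---|---|
| Lung cancer itself | yes | yes | yes |
| Management or treatment of diagnosed lung cancer | yes | not named | yes |
| Work-up of suspected cancer that proves benign | no (a diagnosis is required) | not named | yes |

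The third row is where the direction is clearest. Under section 7.0 placebo subjects have no image taken, so they cannot have a false-positive study screen. The background section lists invasive procedures on benign nodules among the difficulties of the earlier CT cohorts.

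**Screen-detected cancers in the screened arm** (section 14.0 inputs, N = 4000: prevalence 1%, annual incidence 0.5%, sensitivity 85%, compliance 90%, annual loss 10%)

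- Baseline: 4000 × 0.01 × 0.85 = 34.0, or × 0.90 = 30.6 if compliance is applied.
- Incident screen: (4000 − 40) × 0.005 × 0.90 × 0.90 × 0.85 = 13.6.
- Total: 44.2 to 47.6.

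The protocol gives no treatment fatality. If it were 1% to 5% (an assumption), treatment deaths among these cancers would number 44.2 × 0.01 = 0.4 to 47.6 × 0.05 = 2.4.

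**Placebo arm.** Table 2 expects 47.5 advanced-stage cancers, which are treated too. At the same assumed fatality that is 47.5 × 0.01 = 0.5 to 47.5 × 0.05 = 2.4 deaths. The two sets of cancers differ in stage, and probably in treatment, so their difference is not an estimate of net excess. It does show that treatment deaths cannot be placed in the screened arm alone.

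**Effect on the rate ratio.** Assume equal person-years, a true ratio of 1 and D relevant deaths per arm. Omitting s screened and p placebo deaths gives RR = (D − s)/(D − p).

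| D (assumed) | s, p omitted | RR |
|---|---|---|
| 20 | 1, 0 | 19/20 = 0.950 |
| 20 | 3, 1 | 17/19 = 0.895 |
| 20 | 2, 2 | 18/18 = 1.000 |
| 20 | 1, 2 | 19/18 = 1.056 |
| 10 | 3, 1 | 7/9 = 0.778 |
| 30 | 3, 1 | 27/29 = 0.931 |

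The ratio moves towards screening only if more such deaths are omitted in the screened arm. The protocol gives no figure for that excess.

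**The case against.** The strongest reply is that the exclusion is inferred. No sentence says that treatment deaths do not count, and section 13.2 ends person-time at death from lung cancer or its treatment before carrying the analysis over to disease-specific mortality. Inclusion is therefore an available reading, and an analysis plan or committee charter, not seen here, might settle it. This stands against calling the exclusion express. It does not remove the inconsistency, because section 12.2 itself fixes the question put to the committee.

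Second, the division between endpoints is partly declared: section 3.2 wants disease-specific mortality for comparison with other trials and gives screening-related deaths to all-cause mortality. That is a fair reason to keep a strict lung cancer line. But all-cause mortality is a diluted comparison, and it does not repair the cause-specific one.

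Third, any shift would be hard to see. With 20 deaths per arm (assumed), the standard error of ln(RR) is about √(1/20 + 1/20) = 0.316, so the 95% limits lie a factor of exp(1.96 × 0.316) = 1.86 either side. This stands as to size; it is no reason to leave the definition open.

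A reader might go further on two points that the document does not support.

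- That complications are recorded only after a cancer diagnosis, because section 10.0 says that if "the subject is diagnosed with lung cancer additional follow-up will be obtained regarding the diagnosis, pathology staging, treatment, complications and mortality". All subjects also complete six-monthly follow-up and utilization forms, Table 1 lists a nodule form at every visit type, and the case report forms are not shown.
- That the monitoring committee never sees the harms of work-up. Section 17.0 has it review interim analyses as well as adverse events, and their content is not described.

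**Conclusion.** The point holds as an inconsistency in an endpoint definition. Read literally, section 12.2 leaves treatment deaths out of disease-specific mortality, and no cause-specific endpoint takes in deaths from work-up of a suspected cancer that proves benign. Because screening adds work-up and early treatment, this could favour the screened arm.

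A reader might infer that the endpoint is biased towards screening as a matter of fact. The document does not support that. Treatment deaths occur in both arms, no fatality or mortality figures are given, and an equal omission leaves the ratio at 1.00. The net effect may be small or zero. The ratios shown rest on assumed counts of deaths and illustrate scale only. The primary endpoint, the frequency of advanced-stage cancer, is not affected. The change is worth making because it costs almost nothing and closes off a possible bias.

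**What to change.** In section 12.2, define a disease-specific death as: *death due to lung cancer, or to the diagnostic work-up, management or treatment of diagnosed or suspected lung cancer*. Have the blinded committee apply it in both arms without reference to whether the finding came from a study screen. The definition should not mention screen findings, since the committee is blinded to screening results and such a label would reveal the arm. Report deaths strictly due to lung cancer as a second line, which keeps the comparison with other trials that section 3.2 wants. In section 13.2, state that this definition applies when the analysis is carried over to disease-specific mortality.

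The cost is a sentence in 12.2, a cross-reference in 13.2 and one extra line in a results table. The committee already reviews all deaths, so no new review is needed. The downside is that the endpoint may look slightly less favourable to screening.

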The following assumptions were made for determining the required sample size for the primary study aim: prevalence of cancer at baseline screen=1%; annual incidence of cancer=0.5%; annual lost to follow-up=10%; 90% of people randomized to screening are compliant at each screening; 12-month recruitment period; 1 incident screen planned for 12 months after the initial prevalence screen; and 85% sensitivity of chest x-ray with CAD. For development of symptoms following the development of preclinical disease, we assume a uniform distribution over 30 months so that the average time is 16 months from development of detectable preclinical disease until development of symptoms. We assume a 70% reduction in the development of advanced-stage cancers if preclinical disease is detected at screening.

*Placebo Arm:*

Based on these assumptions, if N patients are randomized to the placebo arm, then after one year the number of symptomatic, advanced-stage cancers will be:

(1-lost-to-follow-up rate)(prevalence) (rate of development of symptoms over 12 months)(N).

Similarly, at year two the number of symptomatic, advanced-stage cancers will be approximately:

(1-lost-to-follow-up rate)2 (prevalence) (rate of development of symptoms over 24 months)(N)

for those with preclinical disease at the time of enrollment.

In addition, there are

(1-lost-to-follow-up rate)(incidence)(rate of development of symptoms over 12 months)(N’)

symptomatic, advanced-stage cancers from those who develop lung cancer within the first year, where N’=N-(N)(prevalence).

*Screened Arm:*

If N patients are randomized to the screening arm, and if we assume that at the time of baseline screening, 30% of detected preclinical disease is advanced-stage cancer, then the number of detected advanced-stage cancers detected at baseline is M, where

M = (prevalence)(sensitivity) (0.30)(N).

After one year the number of advanced-stage cancers will be approximately:

(1-lost-to-follow-up rate) (prevalence)(sensitivity)(rate of development of symptoms over 12 months) (N-M)(1-risk reduction due to early treatment) for those cancers detected at baseline but still progressed to symptomatic, advanced-stage cancers in one year.

In addition, there are those cancers undetected at baseline that progress to symptomatic, advanced-stage cancers in the first year:

(1-lost-to-follow-up rate)(prevalence)(1-sensitivity) (rate of development of symptoms over 12 months)(N-M).

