At the one-year incident screen we assume that 15% of detected preclinical disease is advanced-stage cancers. Thus, at the incident screen, M’ advanced-stage cancers will be detected:

M’= (1-lost-to-follow-up rate)(compliance rate with screening)(incidence rate)(sensitivity) (0.15)(N’).

At year two, the number of symptomatic, advanced-stage cancers will be approximately:

(1-lost-to-follow-up rate)2 (prevalence)(sensitivity) (rate of development of symptoms over 24 months)(N-M)(1-risk reduction due to early treatment) for those with preclinical disease detected at the time of enrollment but still progressed to advanced-stage cancers by two years.

In addition, there are those cancers undetected at baseline that progress to symptomatic, advanced-stage cancers over 24 months: (1-lost-to-follow-up rate)2 (prevalence)(1-sensitivity) (rate of development of symptoms over 24 months)(N-M).

There are also cancers that developed over the first year, were detected at the incident screen, and became symptomatic, advanced-stage cancers during the second year:

(1-lost-to-follow-up rate)2 (compliance rate with screening)(incidence)(sensitivity)(rate of development of symptoms over 12 months)(N’-M’)(1-risk reduction due to early treatment).

Finally, there are cancers that developed over the first year, were undetected at the incident screen, and became symptomatic, advanced-stage cancers during the second year:

(1-lost-to-follow-up rate)2 (incidence)(1-sensitivity)(rate of development of symptoms over 12 months)(N’-M’).

Table 2 summarizes the number of advanced-stage lung cancers expected in the two study arms as a function of N.

| N, # subjects per study arm | # advanced-stage cancers in placebo arm | # advanced-stage cancers in screening arm | Total Number of advanced-stage cancers |
| --- | --- | --- | --- |
| 3000 | 35.6 | 23.2 | 58.8 |
| 3500 | 41.6 | 27.1 | 68.7 |
| 4000 | 47.5 | 30.9 | 78.4 |
| 4500 | 53.4 | 34.7 | 88.1 |
| 5000 | 59.3 | 38.7 | 98.0 |

We plan to fit a logistic regression model to describe the probability of advanced-stage lung cancer as a function of 1) patient age, 2) gender, 3) symptoms status at time of enrollment, and 4) study arm randomized to. We will also consider in the model all two-way interactions with study arm. The rule of thumb to avoid model overfitting is at least 10 events per independent variable in the model, thus we need at least 70 advanced-stage cancers (total) for the model building.

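### The primary null is worded on stage at diagnosis, but the sample size also counts screen-detected cancers that later become advanced, so the event tested may not be the event sized

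*Protocol*

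**What the plan says.** **Section 13.1** sets the primary null as "at the time of diagnosis the frequency of advanced-stage cancers is the same for screened and unscreened groups". The alternative hypothesis in the same sentence does not repeat the reference to diagnosis.

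**Section 3.1** speaks of the frequency of advanced-stage cancers as it stands at study end.

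**Section 12.1** says: "The primary outcome measure is the frequency of advanced-stage cancers detected during the course of the 2 ½ year study". Advanced means stage III or IV. One listed route to detection is "through progression of preclinical disease to clinical symptomatic disease". It does not say whether a cancer diagnosed early that later reaches stage III or IV is an event.

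**Section 12.2** carries a note, expressly for the primary and the secondary endpoints, that subjects whose lung cancer has metastasized are censored and are not events.

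**Section 14**, screened arm, counts three groups of cancers that were already diagnosed by screening:

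- "for those cancers detected at baseline but still progressed to symptomatic, advanced-stage cancers in one year"
- "for those with preclinical disease detected at the time of enrollment but still progressed to advanced-stage cancers by two years"
- cancers of the first year that "were detected at the incident screen, and became symptomatic, advanced-stage cancers during the second year"

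Table 2 and the rates of 1.19% and 0.77% used for power include these groups.

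**The concern.** If stage is fixed at diagnosis, a cancer that screening finds at stage I or II stays a non-event even if it reaches stage III or IV before the study ends. Under section 14 the same cancer is an event. The choice affects one arm only, because in the section 14 model every placebo event is first found as symptomatic advanced disease.

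Two things are at stake. First, two analysts who follow this protocol could report different primary results. Second, the stage-at-diagnosis count credits screening with every early diagnosis, including those where treatment did not stop progression. The same tumour in the placebo arm would be found late and counted.

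**Working it through.** **Inputs (section 14).** Prevalence 0.01; annual incidence 0.005; retention 0.9 per year; compliance 0.9; sensitivity 0.85; symptoms uniform over 30 months, so 12/30 = 0.4 by 12 months and 24/30 = 0.8 by 24 months; risk reduction 70%, so a factor of 0.3 remains; advanced share of detected disease 0.30 at baseline and 0.15 at the incident screen. N = 4,000 and N' = 4,000 − 40 = 3,960.

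**Step 1. Reproduce Table 2.**

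Placebo:
- Year 1: 0.9 × 0.01 × 0.4 × 4,000 = 14.40
- 24 months: 0.81 × 0.01 × 0.8 × 4,000 = 25.92
- Incident: 0.9 × 0.005 × 0.4 × 3,960 = 7.13
- Sum 47.45 (Table 2: 47.5)

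Screened, with N − M = 3,989.8 and N' − M' = 3,957.96:

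| Term | Calculation | Events |
|---|---|---|
| M, advanced at baseline screen | 0.01 × 0.85 × 0.30 × 4,000 | 10.20 |
| Detected, progressed, year 1 | 0.9 × 0.01 × 0.85 × 0.4 × 0.3 × 3,989.8 | 3.66 |
| Undetected, year 1 | 0.9 × 0.01 × 0.15 × 0.4 × 3,989.8 | 2.15 |
| M', advanced at incident screen | 0.9 × 0.9 × 0.005 × 0.85 × 0.15 × 3,960 | 2.04 |
| Detected, progressed, 24 months | 0.81 × 0.01 × 0.85 × 0.8 × 0.3 × 3,989.8 | 6.59 |
| Undetected, 24 months | 0.81 × 0.01 × 0.15 × 0.8 × 3,989.8 | 3.88 |
| Incident detected, progressed | 0.81 × 0.9 × 0.005 × 0.85 × 0.4 × 0.3 × 3,957.96 | 1.47 |
| Incident undetected | 0.81 × 0.005 × 0.15 × 0.4 × 3,957.96 | 0.96 |
| **Sum** | | **30.97** (Table 2: 30.9) |

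So Table 2 does include the progression terms.

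**Step 2. Remove the progression terms as printed.** With unrounded terms they sum to 11.73, which is 38% of 30.97. The screened arm becomes 30.97 − 11.73 = 19.24. The reduction against placebo moves from 1 − 30.97/47.45 = 35% to 1 − 19.24/47.45 = 59%. The total falls from 78.4 to 66.7, below the 70 events that section 14 requires for its model.

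**Step 3. Remove two overlaps in the printed terms.**

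(a) The 24-month terms use 0.8, which includes the first 12 months already counted. The second year should add only 0.4.

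(b) The progression terms subtract M from the number of subjects, not from the detected cancers. They therefore cover nearly all 34 baseline-detected cancers (0.01 × 0.85 × 4,000), including the 10.2 already counted as advanced in M. Only 34 − 10.2 = 23.8 are early. At the incident screen, 85% are early.

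- Placebo: 14.40 + 0.81 × 0.01 × 0.4 × 4,000 + 7.13 = 14.40 + 12.96 + 7.13 = 34.5
- Screened, progression: 0.9 × 23.8 × 0.4 × 0.3 = 2.57; 0.81 × 23.8 × 0.4 × 0.3 = 2.31; 0.85 × 1.47 = 1.25; sum 6.13
- Screened, other terms: 10.20 + 2.15 + 1.94 (half of 3.88) + 2.04 + 0.96 = 17.3
- Screened with progression: 17.3 + 6.13 = 23.4

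Reductions: 1 − 23.4/34.5 = 32% with progression; 1 − 17.3/34.5 = 50% without. Progression is 6.13/23.4 = 26% of screened-arm events. The totals are 57.9 and 51.8, so on these counts the minimum of 70 is missed under either definition.

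**Step 4. Effect on power.** Unadjusted comparison of two proportions, 4,000 per arm, two-sided 5%: z = (p1 − p2)/√[(p1(1 − p1) + p2(1 − p2))/4,000] and power = Φ(z − 1.96).

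| Counts, placebo vs screened | z | Power |
|---|---|---|
| Printed, with progression (47.45 vs 30.97) | 1.87 | 46% |
| Printed, without (47.45 vs 19.24) | 3.47 | 93% |
| Overlaps removed, with (34.5 vs 23.4) | 1.46 | 31% |
| Overlaps removed, without (34.5 vs 17.3) | 2.40 | 67% |

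The 77% stated in section 14 does not follow from its own rates by this formula. That is a separate matter; what counts here is how far the definition moves the result.

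**The case against.** **The reading of 13.1.** A reader might infer that 13.1 settles the endpoint as stage at diagnosis and so builds a bias into the trial. The documents do not support that. The phrase occurs once, in the null clause, and the alternative omits it. Sections 3.1 and 12.1 refer to the study period as a whole. What stands is an unresolved conflict between sections.

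**The size.** A reader might also take 31 falling to 19 as the effect of the definition. Those figures follow from the printed formulas, but the deleted terms overlap in time and include cancers already counted in M and M'. With both overlaps removed, about 6 events turn on the definition, not about 12. The direction is unchanged.

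**Stage at diagnosis is a legitimate measure.** The abstract presents size and stage as intermediate outcomes, and stage at diagnosis counted over all randomised subjects is coherent for that purpose. Later harm is covered by the secondary comparisons of symptomatic advanced cancer, lung cancer death and all-cause death. This stands, provided that section 14 sizes the same event and the result is not read as prevention of advanced disease.

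**Counting progression has its own weakness.** Section 10.0 lists pathology staging among the 2-monthly items, but not progression or restaging. That follow-up starts only after diagnosis, and screening brings diagnosis forward, so progression may be sought more intensively in the screened arm. This would act against screening, and it also stands.

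**Conclusion.** The conflict holds: the null is worded on stage at diagnosis, the sample size counts later progression as well, and nothing else in the protocol decides between them. On section 14's own assumptions with the overlaps removed, the screened arm has about 23.4 or 17.3 events against 34.5 on placebo, an apparent reduction of 32% or 50%. As printed, the figures are 31.0 or 19.2 against 47.4. The stage-at-diagnosis reading is the more favourable to screening in both versions.

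The sizes rest on the planning values in section 14, on the 12-month and 24-month symptom fractions of 0.4 and 0.8 that reproduce Table 2, and on applying the 70% risk reduction to early detected cancers only. They are design expectations, not an estimate of bias in observed data. This should be corrected before the primary analysis, but it does not show that the primary result will be biased.

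**What to change.** Use one primary event definition in sections 3.1, 12.1, 12.2 (the note on metastasized cancer), 13.1 and 14.

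**To match the event that was sized:** define it as the first confirmed stage III or IV lung cancer from randomisation to 31 March 2011, at diagnosis or on later progression, in any randomised subject. Delete the reference to the time of diagnosis in 13.1. Reconcile the 12.2 note so that stage IV disease is not excluded from an endpoint that names it. Report stage at diagnosis as a supporting analysis. Restate section 14 with the two overlaps removed.

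**If stage at diagnosis is kept:** say so in every section, remove the three progression terms from section 14, restate Table 2, the rates and the power, and do not interpret the result as prevention of advanced disease. The 12.2 note needs the same reconciliation.

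**Cost.** Wording, a recalculation of section 14 and, for the first option, a progression field on the follow-up form. Progression is recorded less uniformly than stage at diagnosis and may be ascertained more intensively in the screened arm, so the form must record it in the same way in both arms.
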